### Blinding

In this study, many efforts will be done to maintain blinding in participants assigned to the verum acupuncture and sham acupuncture groups. For example, eligible patients will be acupuncture naive, we will set up the standardized ritual operations in the two groups as far as possible. However, patients in the usual care group will not be blinded. They will be provided with 15 sessions of manual acupuncture treatment for free after a waiting period of 7 menstrual cycles. This will increase the compliance of patients allocated to the usual care group. In addition, the acupuncturists will not be blinded.

We will try to ensure that the outcome assessors and statisticians are unaware of the group allocation by (1) using A, B, and C to label the three groups, (2) will randomly assign outcome assessors to follow-up, (3) allocation sequence will be concealed until the end of the study. In addition, we will separately give relevant data of MASS, AEs, and AES to an independent statistician for analysis, while the statistician responsible for the analysis of primary outcome and other secondary outcomes will be blinded to group allocation.

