**Methods/design:**

This is a three-arm, randomized, controlled clinical trial in which the patients, assessors, and statisticians will be blinded. A total of 300 acupuncture-naive patients who were diagnosed as PD will be randomly allocated to the verum acupuncture, sham acupuncture, or usual care groups in a 2:2:1 ratio. Patients in the verum acupuncture group will receive manual acupuncture at specific acupuncture points with penetrating needling, while those in the sham acupuncture group will receive non-penetrating needling at non-acupuncture points. They will be given five sessions over a menstrual cycle for 3 menstrual cycles. Patients in the usual care group will receive health education and informed to receive manual acupuncture for free after waiting for 7 menstrual cycles. The primary outcome will be the change from baseline in the Cox Menstrual Symptom Scale Score (CMSS). The secondary outcomes will be the changes in Massachusetts General Hospital Acupuncture Sensation Scale (MASS), visual analog scale (VAS), Short-Form McGill Pain Questionnaire 2 (SF-MPQ-2), Pittsburgh Sleep Quality Index (PSQI), Beck Anxiety Inventory (BAI), Beck Depression Inventory II (BDI- II), Acupuncture Expectancy Scale (AES), 60-item NEO Personality Inventory-Short Form (NEO-FFI), and acute medication intake. The adverse events will be recorded at every visit. The analyses will be performed base on a full analysis set (FAS) and a per-protocol set (PPS).

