### Sham acupuncture

For the sham acupuncture group, Streitberger placebo needles will be applied at 510 non-acupuncture points, located bilaterally on the back, at a distance of 5 cun lateral to the sixth, seventh, eighth, ninth, and tenth thoracic spine, respectively. No meridians pass through the location of these non-acupuncture points. Because the Streitberger placebo needle is non-penetrating, the acupuncturist will fix a small plastic ring over the point, and then stick the needle through the plaster inside the ring. This will fix the needles on the surface of these non-acupuncture points. Other acupuncture rituals will be identical to the verum acupuncture group.

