### Sample size

The sample size was estimated using the Statistical Analysis System software program (version 9.3; SAS Institute Inc., Cary, NC, USA). According to our pilot trial, we anticipate a greater CMSS score decline of 0.2 ± 0.55 in the verum acupuncture group compared with the sham acupuncture group. This sample size calculation is based on a superiority design with a power level of 80% and a significance level set at 5%, with a 1:1 ratio. Based on these assumptions, 170 patients will be needed, with 85 patients in each group. Moreover, we anticipate a greater CMSS score decline of 0.5 ± 1.15 in the verum acupuncture group compared with the usual care group. This sample size calculation is based on a superiority design with a power level of 80% and a significance level set at 5%, with a 2:1 ratio. Based on these assumptions, 150 patients will be required, including 100 patients in the verum acupuncture group and 50 patients in the usual care group. This sample size will be inflated to 300 to account for an attrition rate of 20%. Thus, we plan to enroll 300 patients, including 120 patients in the VA and SA groups and 60 patients in the usual care group.

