### Allocation

After completing a baseline evaluation, eligible participants will be randomly allocated to the verum acupuncture group, the sham acupuncture group, or the usual care group in a 2:2:1 ratio by an independent investigator. The 2:2:1 ratio was used to facilitate recruitment and increase the compliance of patients. The randomization sequences will be generated in a centralized manner via an interactive web response system with stratified centers and block size of 5. The independent investigator will provide the random sequence and group assignment immediately to the project acupuncturist within opaque, sealed envelopes. To prevent selection bias, the acupuncturists will be the only persons to know the patient’s group assignment prior to treatment. Central randomization has strict limits regarding authority; no one can check the files except the top principal investigator.

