## Discussion

Manual acupuncture is a non-pharmacological treatment that is extremely effective for pain relief and usually performed by traditional Chinese acupuncturists in clinics. Since acupuncture was proposed as a therapeutic intervention for 43 pain conditions by the NIH consensus, the analgesic effect of acupuncture has become more accepted in the Western countries. The underlying mechanisms on acupuncture analgesia maybe involving the release of endogenous opioids, cannabinoids, and adenosine at the central and peripheral systems [12–14].

Recently, a large body of evidence supports the efficacy and safety of acupuncture for the management of PD [28, 29]. This evidence gave rise to a global effort to develop a new generation of treatment options for patients with PD. But so far, high-quality clinical evidence for the role of acupuncture in PD is still insufficient because many clinical trials have had small sample sizes, short follow-up, or other methodological limitations. This study is designed to clarify the efficacy and safety of manual acupuncture for the prevention of PD and to identify the efficacy of acupuncture due to the specific effects of acupuncture or placebo effects of acupuncture ritual. This trial has the strengths of large sample sizes and extended follow-up. The design of the study also meets the methodological benchmarks with valid control, adequate randomization and allocation concealment procedures, and blinding of outcome assessors and statisticians.

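### Arm letters A, B and C cannot hide usual care from the primary-outcome statistician under 2:2:1 allocation, so statistician masking covers verum versus sham at most

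*Protocol article*

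**What the plan says.** The Abstract describes a "randomized, controlled clinical trial in which the patients, assessors, and statisticians will be blinded". The Discussion lists "blinding of outcome assessors and statisticians" among the methodological benchmarks the design meets.

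The Blinding section gives the mechanism. It opens with "We will try to ensure that the outcome assessors and statisticians are unaware of the group allocation" and names three measures: "using A, B, and C to label the three groups", random assignment of assessors to follow-up visits, and keeping the sequence hidden until the study ends. It declares usual-care patients and acupuncturists unblinded. It sends the MASS, adverse-event and AES data to a separate statistician, and says the statistician for the primary and remaining secondary outcomes is blinded to allocation.

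Patients are allocated "in a 2:2:1 ratio by an independent investigator" (Allocation), in blocks of 5 stratified by centre. The Sample size section plans for 300 patients, "including 120 patients in the VA and SA groups and 60 patients in the usual care group". Sham needles go to "non-acupuncture points, located bilaterally on the back" (Sham acupuncture). All the verum points in Table 1 are on the abdomen or legs.

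**The concern.** A letter code hides an arm only if nothing else in the file distinguishes the letters. Here one arm is half the size of the others by design, so the code does not hide it. Verum versus usual care is one of the two contrasts in the Sample size section, and for that contrast the stated blinding of the primary-outcome statistician is a property the design does not have.

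What is at stake is the protection that masking should give to decisions made after data arrive: handling of doubtful diary entries, membership of the analysis sets, and choice of model. That last choice is partly open in the article, because Statistical methods names a Wilcoxon rank-sum test for the CMSS and also an ANOVA with baseline as a covariate and a centre effect.

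The second issue is conditional. The letters are listed as a measure for assessors as well as statisticians. A code shared by a whole arm passes on any single disclosure to everyone with that letter; a patient number does not.

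**Working it through.** **Arm sizes.** From the 2:2:1 ratio (Allocation) and 300 patients (Sample size): 300 × 2/5 = 120, 300 × 2/5 = 120, 300 × 1/5 = 60. This reproduces the plan's figures.

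**After attrition.** The plan inflates the sample to "account for an attrition rate of 20" per cent. Taking that rate in each arm: 120 × 0.8 = 96, 120 × 0.8 = 96, 60 × 0.8 = 48. Usual care is still half the size of each other arm.

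**Can chance hide the small arm?** Completers were simulated as Binomial(n, 1 − d) in each arm, with 200,000 runs. The attrition rates other than 20% are assumptions.

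| Attrition d | Probability that usual care is strictly the smallest letter |
|---|---|
| 0%, 10%, 20% or 30%, equal in all arms | 1.00 |
| 40% in both needled arms, 0% in usual care (deliberately extreme) | 0.97 |

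**What would make the sizes equal?** If usual care lost nobody, a needled arm would have to fall from 120 to 60, a loss of 60/120 = 50%. If usual care had fallen to 48, a needled arm would have to lose 120 − 48 = 72, and 72/120 = 60%.

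**A second route to the same knowledge.** Statistical methods applies an ANOVA to the two intervention groups. If these are verum and sham, whoever runs it must know which two letters are needled, and so which one is usual care.

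**What size does not reveal.** Verum and sham are both planned at 120, so size does not separate them.

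**Conditional step, only if assessors see letters.**
- Three letters can map to three arms in 3! = 6 ways.
- Once usual care is known (by size, or because those patients are open), 2 ways remain.
- One needled patient who says whether the needles went into the back, or into the abdomen or legs, leaves 1. That decodes all 120 + 120 = 240 needled patients.
- With patient numbers only, the same remark reveals 1 of 240 (0.4%).

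**The case against.** **The assessor route rests on a premise the article does not state.** Nothing says a patient's letter appears on anything an assessor handles. The three measures are listed jointly, and a fair reading is that the letters serve the analysis file while random assignment serves the assessors. The content of follow-up forms is also something an article leaves to the full protocol. This stands. A reader might infer that one remark will unmask every verum and sham patient; the documents do not support that. The 240-of-240 figure holds only if assessors see the letters.

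**Verum versus sham is not exposed by size.** This also stands. A reader might infer that the statistician's masking fails altogether, but the needled arms are equal and a statistician does not normally meet patients, so a remark about needle site would not usually reach that role.

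**Any labelling of grouped 2:2:1 data shows the smaller arm.** True, and no fix removes it. But the text claims the opposite without qualification, and the claim can be corrected.

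**The plan already handles part of this.** It calls usual care unblinded, says only that it will try, and diverts MASS, adverse events and AES, which usual care does not supply. That removes some obvious markers but not arm size. A reader might add that the compliance comparison reveals usual care. Statistical methods gives only an 80–120% range and does not define compliance as session attendance, so the point does not rest on it.

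**The consequence is small.** Data collection and management says the primary outcome comes from the patient's diary, so assessors have little room to influence the CMSS. No bias or error rate has been shown. This stands and keeps the point minor.

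**Conclusion.** The point holds for the statistician. At 120:120:60, or 96:96:48 after 20% attrition in each arm, the smallest letter is usual care with practical certainty. The primary-outcome statistician is therefore masked at most to verum versus sham, and the unqualified statements in the Abstract, Blinding section and Discussion are wrong for verum versus usual care. This assumes only that the statistician receives data grouped by letter and knows the published ratio.

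For assessors the point is conditional on their seeing the letters. If they do, one disclosure can spread to the other needled patients; if they do not, it stays with one patient. Either way the effect on the diary-based CMSS is limited. The Abstract's claim that patients are blinded also needs reconciling with the Blinding section, which excepts usual care. Overall this is a minor point about an overstated safeguard, and not evidence of a biased result.

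**What to change.** - **Blinding section:** state that assessor and data-entry records carry patient numbers only, and that arm letters are attached only when the analysis file is made at database lock.
- **Analysis program:** fix it before any arm-labelled data are released, including whether the Wilcoxon test or the ANOVA is primary for the CMSS. If a statistical analysis plan already does this, a reference to it is enough.
- **Session attendance:** send any such data to the separate statistician who already receives MASS, adverse events and AES.
- **Abstract, Blinding section and Discussion:** state that usual care is open to patients and identifiable to the statistician by size, so that statistician masking covers verum versus sham only.

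The cost is a slightly weaker blinding statement and minor data-handling work. No patients or staff are added, and the allocation ratio and treatments stay as they are. Trial status reports enrolment still in progress at submission, so the database-lock steps and the wording could still be changed at that time.

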### Data collection and management

Demographic and epidemiological data will be obtained at visit 1, using a general information questionnaire. The questionnaire includes information on age, gender, education, occupation, weight, height, previous disease history, history of PD, and menstrual cycle. If the participants are assessed eligible, they will be asked to record dysmenorrhea diary from menstrual cycle 1 before randomization to menstrual cycle 6 after randomization. All of the primary outcome measures and most of the secondary outcome measures will be obtained from the dysmenorrhea diary. The dysmenorrhea diary includes questionnaires on CMSS, VAS, SF-MPQ-2, PSQI, usage of acute medication, BAI, BDI- II, and NEO-FFI. The diary will be separately collected from the participating hospitals every menstrual cycle. Data of AEs and MASS will be recorded on acupuncture report forms by patients after each treatment. The data will be collected up to the time of withdrawal and will be included in the analysis unless participants specifically request for their data to be withdrawn.

Data management will be ensured by an electronic data capture (EDC) system hosted at the Data Management Center of Tongji Hospital. All paper-based data will be checked and input into the EDC system by two research assistants using a separate account and password. After that, paper-based data will be stored in a locked file cabinet in the principal investigator’s office at the Department of Neurology of Tongji Hospital. The electronic data will be stored at the EDC system after being approved by an electronic signature. After approval of a proposal and with a signed data access agreement, researchers whose proposed use of the data has been approved can access the data. Independent randomization, rigorous blinding, and data management make sure the confidentiality of this trial.

### Monitoring and quality control

To guarantee the quality of the study, unified training before subject recruitments will ensure the researcher’s adherence to the study protocol. Strict eligible criteria limit the study population to a specific scope and reduce the differences among them. A web-based central randomization system is adopted to avoid selection bias. Independent outcome assessment and statistics are designed to guarantee the objectivity of the data.

Quality control of the data will be handled at three different levels. The first level is the quality check of sub-centers regularly by the head of the sub-center. The second level is the quality inspection by the Clinical Research Center of Tongji Hospital, at least once per 3 months. The third level is the quality monitor by the Clinical Evaluation Center of Hubei University of Chinese Medicine, at least once per 6 months.

Treatment safety is based on the assessment of AEs and serious adverse events (SAEs). An event can be defined as an adverse event if subjects suffer a symptom related to acupuncture, which includes unbearable acupuncture pain, palpitation, fainting, dizziness, sweating, needle broking, needle body wound muscle fiber, bleeding at the acupuncture site, and local hematoma. All subjects will be informed of the potential AEs before signing the informed consent. If any AEs occur during the study periods, they will be recorded in detail on the CRF. The researcher should record the following details: the date, the time, the symptoms, and the degree of occurrence related to the treatment at each visit, and provide proper medical advice and care. In order to ensure the safety of subjects, a Data and Safety Monitoring Board (DSMB) was set up to monitor the performance and safety of the trial, which is composed of 5 experts from different fields on the Chinese mainland. If any serious adverse events occur, they will be immediately reported to the DSMB, although SAEs will not be anticipated.

## Discussion

Manual acupuncture is a non-pharmacological treatment that is extremely effective for pain relief and usually performed by traditional Chinese acupuncturists in clinics. Since acupuncture was proposed as a therapeutic intervention for 43 pain conditions by the NIH consensus, the analgesic effect of acupuncture has become more accepted in the Western countries. The underlying mechanisms on acupuncture analgesia maybe involving the release of endogenous opioids, cannabinoids, and adenosine at the central and peripheral systems [12–14].

Recently, a large body of evidence supports the efficacy and safety of acupuncture for the management of PD [28, 29]. This evidence gave rise to a global effort to develop a new generation of treatment options for patients with PD. But so far, high-quality clinical evidence for the role of acupuncture in PD is still insufficient because many clinical trials have had small sample sizes, short follow-up, or other methodological limitations. This study is designed to clarify the efficacy and safety of manual acupuncture for the prevention of PD and to identify the efficacy of acupuncture due to the specific effects of acupuncture or placebo effects of acupuncture ritual. This trial has the strengths of large sample sizes and extended follow-up. The design of the study also meets the methodological benchmarks with valid control, adequate randomization and allocation concealment procedures, and blinding of outcome assessors and statisticians.

The form of acupuncture used in this trial is manual acupuncture treatment, which will be performed by licensed traditional Chinese acupuncturists. After the acupuncture needle is inserted into the acupoints, the manual manipulation of the needle will generate *de qi* sensations and enhance the clinical benefit of acupuncture analgesia. This may be due to the activation of the pain-inhibiting system in the spinal cord and diffuse noxious inhibitory controls (DNIC) [30, 31]. The intensity of *de qi* sensation is critical for the effects of acupuncture [32]. Our earlier study showed that among patients with Bell palsy, acupuncture with strong stimulation that elicited *de qi* had a greater therapeutic effect, and stronger intensity of *de qi* was associated with better therapeutic effects [33]. However, the important concept of *de qi* sensations has been neglected in acupuncture research in Western countries. This may be due to the difficulty to quantitatively measure complex *de qi* sensations in acupuncture research. In this study, we will use the MASS to quantify the intensity of *de qi* sensations after each treatment. Using the MASS, we will explore the association between the intensity of *de qi* sensations and changes in efficacy outcomes. As far as we know, this is the first acupuncture trial to quantify the measure *de qi* sensations in a patient population of PD.

Appropriate control is one of the largest methodological challenges in acupuncture research. So far, most of the clinical trials used penetrating sham acupuncture to control the specific effect of acupuncture, including superficial needling, needling non-specific acupoints, or needling non-acupoints. However, it is increasingly regarded that penetrating sham acupuncture is not a proper control method because it was not totally inert [34]. An advantage of this trial is the use of non-penetrating sham acupuncture with the Streitberger placebo needle, which could mimic an acupuncture procedure without penetrating the skin. It is designed for subject blinding and sufficiently credible to investigate the effects of acupuncture [35], since the spinal segmental relationship between pain sites and acupuncture points partially underlies the functional specificity of acupoints. Consequently, we apply sham acupuncture at ten non-acupuncture points on the back which is beyond the uterus segment to highlight the functional specificity of acupoints in the verum acupuncture treatment group.

Many psychological factors are regarded as risk factors of dysmenorrhea and should be considered in the management of dysmenorrhea [36, 37]. A study indicated the important impact of depression and anxiety on menstrual symptoms among non-smokers patients [38]. In addition, the placebo effects of acupuncture observed in sham-controlled clinical trials may be referred to the psychological benefits of treatment, including acupuncture ritual, expectation, and explanation [26, 39], while depression, anxiety, and personality pathology were considered to have negative impacts on the physiological response to acupuncture [39]. For these reasons, we will comprehensively assess the influence of depression, anxiety, expectation for acupuncture, and patient-doctor relationship in this study.

One limitation of this study is that acupuncturists who will deliver the treatment will not be blinded to the intervention. To reduce their effect on patients, acupuncturists will only know the patient’s group assignment just before treatment. Through this rigid research, we anticipate to provide high-quality evidence on the efficacy of acupuncture for the prevention of PD. If effective, it will offer an important treatment option for patients with PD.

